**Figure 1 F1:**
[figure not shown]
Study flow.

Randomization will occur using a form of adaptive randomization called minimization [77,78]. Compared to techniques such as stratification, minimization results in better group balance on participant characteristics. Minimization also provides for balanced treatment groups throughout the randomization process. Randomization will be balanced on gender, age, immigrant status, cigarettes per day, and BMI.

Individuals randomized to the MAPS condition will schedule their first counseling call during the baseline visit, and subsequently receive up to 18 counseling calls over an 18-month period. Outcome assessments will occur at baseline, 6 months, 12 months, and 18 months. Also after completing the assessment and randomization procedures, the 6-month follow-up visit will be scheduled for all participants. Research staff conducting the outcome assessments will be blinded to participants’ treatment conditions.

### Control and treatment conditions

#### HE condition

HE will include three sessions of brief advice (10 minutes) regarding smoking cessation, diet, and physical activity change, including the provision of referrals to resources for behavior change (e.g., Texas Quitline, community diet and physical activity programs). Participants will also receive Spanish language self-help materials. Participants will be given a home-based exercise kit (e.g., pedometer, exercise ball, strength training cables) and related instruction on the use of the exercise kit’s content during the first HE session. When the participant informs research staff that s/he is ready to make a smoking cessation attempt, a 6-week supply of free nicotine patches will be provided. HE will occur a total of 3 times (during the in-person assessment appointments at baseline, 6 months, and 12 months).

#### MAPS condition

The treatment condition will include HE plus up to 18 proactive, telephone-delivered MAPS counseling sessions over the 18-month period. Each counseling call will last approximately 20–30 minutes. Call frequency is negotiated between participant and counselor based on a participant’s motivation and needs. For example, several calls might be clustered around the initiation of a walking program, a smoking cessation attempt, holiday diet challenges, or specific barriers that the participant is facing (e.g., stress, lack of social support, family problems, financial crisis). Conversely, calls might be scheduled very infrequently when the participant is doing well. Regardless of when calls have been scheduled, participants are always able to call the study telephone line and request a counseling call.

All participants will complete a Wellness Plan in collaboration with their MAPS counselor. The Wellness Plan is an organization of goals or areas of concern/importance that the participant wants to work on during counseling. Wellness Plan items may include change goals for participants who are ready to make changes. The Wellness Plan may also include areas of concern or other topics that the participant would like to discuss where they may or may not be ready to change. Thus, the Wellness Plan will also be used in work with participants who are not motivated to make changes. This is because, although MI will be the primary task being used in working with these participants, it may be helpful to list areas of concern or topics that the participant is simply willing to explore and revisit. Wellness Plan goals can include not only goals related to the target behaviors, but also a plan for addressing other salient concerns such as stress, interpersonal issues, family problems, etc. The Wellness Plan can also include plans for connecting participants with resources in the community to address their needs, such as vocational and educational training, and free or low cost childcare and medical treatment. The Wellness Plan is a central organizational component of counseling. Thus, although a participant can develop a Wellness Plan as early as the first few sessions, it is revisited and revised over time to reflect participants’ progression through the program or any new areas of emphasis.

MAPS is designed to tailor counseling sessions completely around the participant’s expressed readiness to change a target behavior, and their unique needs and preferences for coping skills. Thus, it is unlikely any two participants will progress through the program at the same pace or express/address identical concerns. However, the general progression is broadly organized as follows: Early MAPS counseling sessions (e.g., 1–5) are intended for introduction to the target behaviors and an assessment of the participant’s motivation to change any or all of smoking, fruit/vegetable consumption, and physical activity. Where the participant expresses readiness, Problem Solving/Skills Training techniques are utilized to facilitate change. Where the participant is not yet ready, a MI approach is utilized. Later sessions (e.g., 7–16) are used either for continued MI in the areas where the client expresses not being ready to change, action oriented counseling to facilitate change, or maintenance of change, Sessions 17 and 18 prepare the participant for ending the program and include a final review of goals and progress, saying good-bye, and providing any additional necessary referrals.

#### Counselor qualifications, calls, and training

MAPS has been developed to be appropriate for delivery by lay and professional health workers. Counselors receive approximately 40 hours of MAPS training initially with “booster” sessions of approximately 1–2 hours every 1–2 months during the study. Training continues until the counselor reaches competence and adherence criteria. Miscellaneous counseling issues are also discussed at weekly project meetings. This level of training and ongoing monitoring is consistent with the recommended level of training for real-world providers of health promotion interventions such as Quitline counselors [79] and ensures that MAPS is of the highest quality and follows the protocol precisely, both of which are key fidelity issues in evaluating new treatments. Counselors will be two Spanish-speaking members of the study staff who are experienced in the delivery of MAPS.

##### Treatment fidelity

To monitor drift, all calls are digitally recorded and encrypted. A random sample of 10% of calls are coded using a modified Motivational Interviewing Treatment Integrity Manual MITI; [80]. The MITI has empirically validated reliability and validity, and is modified to include coding around appropriate social cognitive/problem-solving strategies, and transitions between the motivation building and problem-solving. Because MAPS utilizes a MI framework, the MITI works well for ensuring adherence to the protocol and utilizing the general MI spirit. A counselor who falls below performance criteria will receive additional training.

#### Instruments

The majority of the assessment instruments have been previously used and validated in Spanish, or are being tested in our current research. Assessment instruments measure outcomes or hypothesized mechanisms. We attempted to reduce the inconvenience associated with completing the assessment battery by providing financial compensation for participants’ time and by using the Questionnaire Design System (QDS), a computer-administered self-interview format. The error and time necessary to complete an assessment battery are substantially reduced by using QDS and particularly so among individuals with low literacy because the computer can read each item in Spanish to the participants. Assessment procedures will be identical at each of the four visits, with the exception that only a subset of the demographic measures will be administered at the 6, 12, and 18 month follow ups.

### Primary outcomes

#### Physical activity

##### International physical activity questionnaire (IPAQ)

The IPAQ assesses walking for exercise, walking for transportation, moderate and vigorous physical activity, and time spent sitting. It is widely used to measure physical activity [73].

##### Accelerometer

Participants will wear a small blinded accelerometer (i.e., participant cannot see values) over 7 days to assess physical activity. Accelerometers will be distributed at each assessment visit and will be returned via mail.

#### Fruit/vegetable consumption

##### National health interview survey diet items

Items will be used to assess frequency of food intake in 16 broad categories to estimate intakes of fruits and vegetables, percentage energy from fat, and fiber diets [81].

##### Two-item food frequency questionnaire

The two-item food-frequency questionnaire was developed to estimate intake of fruit and vegetables [82].

#### Smoking abstinence

Assessments will follow the recommendations from the Society for Research on Nicotine and Tobacco for cessation induction trials [83]. Participants will provide breath carbon monoxide to verify smoking. Although carbon monoxide has a relatively short half-life, the most comprehensive review on biochemical validation concluded that misreporting is typically very low (~2%) except for populations with substantial incentives to misreport (i.e., adolescents, pregnant women), and that adjustment for misreporting almost never influences analyses regarding relative treatment efficacy [84]. Participants will also provide a saliva sample to verify smoking status. The saliva sample will be provided at the baseline, 6 month, 12 month and 18 month follow-up visits. Saliva samples will be analyzed for cotinine, a metabolic byproduct of nicotine that provides an estimate of nicotine consumption. A saliva cotinine level of <20 ng/ml will be considered as abstinent.

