### Study population and eligibility

The study population will be overweight or obese Spanish-speaking Mexican- or Mexican-origin smokers who reside in the Houston, Texas, metropolitan area. Inclusion criteria will be: 1) self-report of Mexican heritage; 2) age 18 or older; 3) current smoker with a history of smoking an average of at least one cigarette per day during the last year; 4) register an expired carbon monoxide level of at least five parts per million; 5) body mass index ≥ 25 based on measured height and weight; 6) ability to engage in low to moderate physical activity as determined by the Physical Activity Readiness Questionnaire PAR-Q; [73]; 7) blood pressure reading <140/90 millimeters of mercury (mm Hg); 8) speak Spanish, and; 9) have a valid home address and a functioning telephone number. Participants do not need to be motivated to change their behavior.

Participants with high blood pressure readings defined as ≥ 140/90 mm Hg; [74] and those deemed ineligible based on the PAR-Q will be able to participate if they provide a letter from a physician who will continue to monitor the participant during the research study. Exclusion criteria include: 1) women who are pregnant or currently lactating; 2) contraindication for nicotine patch; 3) other active substance abuse or dependence; 4) regular use of other tobacco products; 5) current use of tobacco cessation medications; 6) currently enrolled in another study; 6) another household member enrolled in the study, and; 6) a score below 38 on the Short Assessment of Health Literacy for Spanish Adults SAHLSA; [75]. Ineligible individuals will be given referrals to community resources.

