### Pharmacotherapy

All study participants will have access to free nicotine patch therapy when they are ready to make a quit attempt. The provision of patch therapy or other cessation medication is the recommended standard of care. As such, it is arguably an ethical obligation to provide all participants with access to patch therapy. Study participants receive nicotine patch therapy because the patch is currently recognized as a frontline therapy [22], and compared to non-nicotine medications such as bupropion or varenicline, the patch is safer, better tolerated, and available over the counter. Participants who decide to make a quit attempt will request patches by contacting project staff. Patches and instructions for their use will be distributed either via a visit to MD Anderson or via the mail. Patch therapy for participants who smoke >10 cigarettes/day will consist of 4 weeks of 21 mg patches, 1 week of 14 mg patches, and 1 week of 7 mg patches. Patch therapy for participants who smoke 6–10 cigarettes/day will consist of 4 weeks of 14 mg patches and 2 weeks of 7 mg patches. Patch therapy for participants who smoke 1–5 cigarettes/day will consist of 6 weeks of 7 mg patches. A reduction in dosage or cessation of the patch regimen will be implemented for any participants who report signs of being on too high of a dose, although this is typically not necessary for participants because blood nicotine levels are usually far lower on the patch than while smoking [91]. In sum, all participants, regardless of treatment group assignment, will have the same access to nicotine patch therapy. We will carefully track pharmacotherapy use at all follow-up assessments.

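### The cotinine cut-off for abstinence makes no exception for nicotine replacement in a trial that supplies patches, so abstainers on patch at a visit can be recorded as smokers

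*Protocol article*

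**What the plan says.** Under Smoking abstinence, the protocol article says that assessments follow a society's recommendations for cessation induction trials. It lists two biochemical measures. The first is expired CO: "Participants will provide breath carbon monoxide to verify smoking". No CO level that counts as abstinent is given. The second is saliva cotinine, taken at all four visits and described as "a metabolic byproduct of nicotine that provides an estimate of nicotine consumption". The section ends with the only abstinence cut-off in the document: "A saliva cotinine level of <20 ng/ml will be considered as abstinent".

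Under Pharmacotherapy, "All study participants will have access to free nicotine patch therapy when they are ready to make a quit attempt", and participants in both arms "will have the same access to nicotine patch therapy". The HE condition section, which also applies to MAPS because MAPS contains HE, sets the amount: "a 6-week supply of free nicotine patches will be provided". Pharmacotherapy use is to be tracked at every follow-up, and the Smoking Status Questionnaire records nicotine replacement.

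The only numerical CO level is an entry criterion: "register an expired carbon monoxide level of at least five parts per million". Nothing shown says how self-report, CO, cotinine and recorded patch use combine into smoking status.

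**The concern.** By the protocol's own description, cotinine reflects nicotine from any source, and the trial supplies nicotine to people who are trying to quit. Courses can start at any point over 18 months. The Binary outcomes section expects 80–90% of participants not to be motivated to quit at baseline, so quit attempts will be spread over follow-up and some courses will overlap a visit. The cut-off as worded cannot separate a non-smoking patch wearer from a smoker.

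Smoking status is a primary outcome and also an outcome in the Aim 2 mediation analysis. If MAPS produces more new quitters, more MAPS participants will be on patch at a visit, and more true successes will be lost from MAPS than from HE in absolute terms.

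**Working it through.** **Inputs from the document.** HE abstinence of 5%, 10% and 15% at 6, 12 and 18 months. MAPS abstinence of 10%, 20% and 30% in the increasing scenario of Table 2, which the Binary outcomes section calls most likely. 160 per arm after attrition; two-sided alpha 0.05; ICC 0.3; a 6-week patch course; visits about 26 weeks apart.

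**Assumptions not in the document.** Every patch wearer is at or above 20 ng/ml. Every quitter uses a full 6-week course. Starts are spread evenly between visits. Abstinence accumulates, so the rise in each interval is the newly quit group. People just off the patch are not counted.

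**Step 1: the plan's own figure.** Test the risk difference averaged over three visits. With s = √(p(1−p)) at each visit, the variance of an arm's mean is [Σs² + 2·ICC·Σ(s_i·s_j)] / (9 × 160).
- HE: Σs² = 0.265, Σ(s_i·s_j) = 0.2503, so the bracket is 0.265 + 0.6 × 0.2503 = 0.4152.
- MAPS: Σs² = 0.460, Σ(s_i·s_j) = 0.4408, so the bracket is 0.460 + 0.6 × 0.4408 = 0.7245.
- SE = √[(0.4152 + 0.7245)/1440] = 0.0281.
- Power = Φ(0.10/0.0281 − 1.96) = Φ(1.59) ≈ 0.945. Table 2 states 0.95.

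This contrast does not match every cell of Table 2. It gives 0.89 against 0.84 for increasing differences at ICC 0.5, for example. The test behind the plan's simulation is not described, and the point does not depend on those cells.

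**Step 2: misclassification.** The share of new quitters on patch at a visit is 6/26 = 0.231. In the increasing scenario each interval adds 5 points in HE and 10 in MAPS. HE therefore loses 5 × 0.231 = 1.15 points and MAPS loses 10 × 0.231 = 2.31 points at each visit, so the difference shrinks by 1.15 points.

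| Visit | True difference | Recorded difference | Relative loss |
|---|---|---|---|
| 6 months | 5.0 | 3.8 | 23% |
| 12 months | 10.0 | 8.8 | 12% |
| 18 months | 15.0 | 13.8 | 8% |

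**Step 3: power.** With recorded rates of 3.85/8.85/13.85% and 7.69/17.69/27.69%, the two brackets are 0.3684 and 0.6519. SE = √(1.0203/1440) = 0.0266, the mean difference is 0.0885, and power = Φ(0.0885/0.0266 − 1.96) ≈ 0.91. If half of quitters use patches, the differences are 4.4/9.4/14.4 points and power is 0.93. An average log-odds contrast, closer to the planned logit model, starts lower (0.88, so it does not reproduce 0.95) and falls to 0.81.

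**Step 4: range.** Let f be the share of all abstainers at a visit who are on patch, equal in both arms. It could exceed the step 2 values if relapse and re-quitting keep refreshing the newly quit group.

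| f | 18-month risk difference | 18-month odds ratio | Risk ratio | Power, ICC 0.3 |
|---|---|---|---|---|
| 0 | 0.150 | 2.43 | 2.00 | 0.945 |
| 0.05 | 0.1425 | 2.40 | 2.00 | 0.93 |
| 0.10 | 0.135 | 2.37 | 2.00 | 0.915 |
| 0.23 | 0.1155 | 2.30 | 2.00 | 0.86 |
| 0.30 | 0.105 | 2.27 | 2.00 | 0.82 |

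**Step 5: unequal f.** With f = 0.05 in HE and 0.15 in MAPS, the 18-month rates become 0.15 × 0.95 = 0.1425 and 0.30 × 0.85 = 0.255, and the risk ratio falls from 2.00 to 1.79. The direction can also reverse. In Table 2's decreasing scenario MAPS stays at 20% while HE gains 5 points per interval, so step 2 would take 1.15 points from HE and none from MAPS at 12 and 18 months.

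**The case against.** The strongest objection is that the cotinine sentence may be the threshold for one assay within a composite. The section cites society recommendations, collects CO, and discusses verification and misreporting, all of which presuppose a self-report. Nicotine-replacement use is recorded. A journal article condenses a longer protocol, which may hold the combining rule. This stands in part: it shows that correct classification is possible with the planned data. It does not remove the difficulty, because the one cut-off the article does state is unconditional, and a general reference to recommendations does not qualify it.

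A second objection is that the document gives no cotinine level on patch. It says only that blood nicotine is usually well below smoking levels, which does not settle whether cotinine passes 20 ng/ml. This stands, and the result is conditional on it.

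Three stronger readings are tempting and are not supported:
- **Patch users in general will be counted as smokers.** Only abstainers on, or just off, a patch at a visit are exposed.
- **The outcome is biased against MAPS on every scale.** With equal on-patch proportions among abstainers the risk ratio does not change and a true null stays null. Access is the same in both arms and no figure for differing uptake is given, although equal access does not guarantee equal uptake.
- **Abstinence needs no self-report.** The cut-off sentence does not mention one, but the surrounding text and the Smoking Status Questionnaire, listed under Primary outcomes, imply a self-report that is being verified.

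**Conclusion.** The point holds in a limited form. As stated, the cut-off can record abstinent patch wearers as smokers on a primary outcome, and nothing shown links CO or recorded patch use to the classification. Under full patch use by all quitters and evenly spread starts, the loss is about 1.2 percentage points at each visit in the increasing scenario. Power falls about 3 points on the contrast that reproduces the plan's figure; lower patch use means a smaller loss. The shift toward the null on the risk-difference and odds-ratio scales requires similar on-patch proportions among abstainers in the two arms; the risk ratio is biased only if those proportions differ. All of this assumes that cotinine on patch reaches 20 ng/ml. A reader might infer that the smoking result would be unusable without a change. The figures do not support that, and the severity is moderate.

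**What to change.** In the Smoking abstinence section, define abstinence at each visit as self-reported abstinence with biochemical confirmation:
- participants reporting no current nicotine replacement: saliva cotinine below 20 ng/ml;
- participants reporting current nicotine replacement: expired CO below a pre-specified cut-off. The sponsor should choose and justify the value; the 5 ppm entry level is the only CO figure now in the document.

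State how a recently finished course is handled. Add a sensitivity analysis that applies the cotinine rule to everyone, and report on-patch proportions by arm and visit so that the size of any difference can be seen. Fix the rule before outcomes are classified, since a later choice would be open to challenge.

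The cost is one paragraph and no new data: CO, cotinine, the Smoking Status Questionnaire and pharmacotherapy use are already collected. The downside is small: CO has a shorter detection window, so confirmation is weaker in the patch-using subset.

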#### Smoking status questionnaire

This surveys tobacco use, use of other tobacco products, and nicotine replacement medications. The questionnaire also collects data on the use of other tobacco products and nicotine replacement medications as determined by the participant's time point in the protocol (e.g., based upon the date the participant quits smoking) [83].

### Measures of hypothesized treatment mechanisms

#### Barriers self-efficacy physical activity

The Barriers Self-Efficacy Physical Activity is a 5-item measure on a five-point Likert-type and measures one’s confidence to meet a physical activity goal in the face of barriers to the behavior [85].

#### Fruits and vegetables self-efficacy

The Fruits and Vegetables Self-efficacy is a 7-item measure on a 5-Likert scales. Items assess family influences, decisional balances, and fruit and vegetable intake [85].

#### Fruits and vegetables staging

This is a 2-item measure of daily intake of fruits and vegetables and intent to change the current intake of fruit and vegetables.

#### Motivation

Motivation to abstain from smoking will be assessed with a 10-item scale currently being developed by our research team in order to assess motivation as a continuous variable as opposed to a stage. Items assess the motivation to quit smoking [86].

#### Positive and negative affect scale (PANAS)

The PANAS is comprised of two mood scales with high reliability, Positive Affect (PA) and Negative Affect (NA) [87].

#### Self-efficacy scale

This is a 9-item scale reflecting the confidence of the individual that they can cope with high-risk situations without smoking [88].

#### Smoking self-efficacy/confidence

The Smoking Self-Efficacy/Confidence scale assesses an individual's confidence to abstain from substance use or health behaviors in a variety of different situations. It consists of 9-item with 5 responses ranging from not at all confident to completely confident [88].

